### Trial design {8}

The GOAL Trial is a pragmatic, multicentre, superiority, open-label cluster randomised controlled trial. While the intervention will be implemented at the participant level, randomisation at the cluster (hospital) level has been chosen to avoid contamination of the intervention. The Australasian Kidney Trials Network (AKTN, The University of Queensland) is the sponsor and coordinating centre for the trial.

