**Secondary objectives**		
To determine whether CGA improves attainments of patients’ own goals of care over time	GAS	Baseline, 3, 6 and 12 months
To determine whether CGA improves patient’s quality of life over time	EQ-5D-5L	Baseline, 3, 6 and 12 months
To determine whether CGA favourably affects the trajectory of frailty status over time	FI	Baseline, 3, 6 and 12 months
To determine whether CGA reduces mortality during the 12-month follow-up	All-cause mortality (time to event, proportion) Cause-specific mortality (time to event and proportion)	Continuous
To determine whether CGA reduces the number of hospital admissions during the 12-month follow-up	Hospital admissions (number and reason)	Continuous
To determine whether CGA reduces the hospital length of stay number during the 12-month follow-up	Hospital length of stay (days)	Continuous
To determine whether CGA reduces admissions to RACF at 12 months follow-up	Time to RACF admission	Continuous
To determine whether CGA is cost-effective within the trial context	Health care use analysis	Continuous

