### Participant timeline {13}

All participants will be followed up by their respective hospitals for a total of 12 months. A SPIRIT [1, 2] diagram for the schedule of enrolment, intervention and assessments is included as Fig. 1. There will be a total of six interactions required for participants at an intervention site and five at control sites. There will be no trial-specific laboratory or radiological investigations requiring visits. Depending on the individual, a geriatrician may request further investigations as part of their CGA and referrals to other specialty services may occur. Upon completion of the trial’s 12-month follow-up, a small group of ~ 30 purposively sampled patients will be approached to participate in interviews for the qualitative data collection required for process evaluation. This interview would necessitate an additional visit.

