### Sample size {14}

Based on data from community-dwelling frail older adults, it is estimated that CGA will improve the GAS score by at least 10 points from an average score of 36 at baseline (which presents a change in one standard deviation, equivalent to a medium effect size) [25].

It is estimated that a cluster randomised trial with an average cluster size of 20 participants (coefficient of variation of sizes = 1) would require 16 hospital sites (clusters) with 8 sites in the intervention and control arm, respectively, to achieve 90% power to detect a mean difference in GAS score of 10 units at 3 months follow-up. This power calculation, giving a sample size of 320, assumes a common standard deviation of 10 units and an intra-cluster correlation coefficient of 0.3. To achieve sufficient power for the analysis of the secondary outcome of GAS at 12 months, an allowance for a 33% loss to follow-up over the 12 months was included, requiring baseline GAS observations from 478 participants. The 16 sites will be expected to each have a minimum of 55 patients who meet the eligibility criteria. Based on previous studies, it is estimated that approximately 10% of eligible patients will not consent to participate [26, 29] and a further 35% will not meet the frailty criteria [38] leaving a recruitment target of 500 (approximately 30 at each site). Assumptions in the sample size calculation will be re-estimated on trial data at the mid-point of the planned recruitment period.

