## Statistical methods

### Statistical methods for primary and secondary outcomes {20a}

Data will be analysed at the individual patient level. The primary outcome, Goal Attainment Scaling (GAS) scores at three months, will be analysed using a linear regression model with the intervention group as a binary covariate and baseline GAS score as a continuous covariate. To allow for the clustering of data within study centres, inference will be based on robust standard errors. Multiple imputation will be used if there is more than 5% missing data on the three-month GAS scores. Subgroup analysis of GAS scores at three months will be undertaken based on baseline characteristics of patients (including age, CKD stage, and frailty status) and study site (including unit size). Subgroup effects will be assessed via treatment-by-subgroup interactions in linear regression models.

Repeatedly measured continuous secondary outcomes (GAS scores at 6 and 12 months, EQ-5D-5L scores, FI) will be analysed using mixed models for repeated measures (MMRM) with a random intercept for the study centres and an unstructured variance–covariance matrix to model the within-patient correlation structure due to the repeated measurements. The models will have fixed effects for the intervention group, categorical time, the intervention-by-time interaction, and baseline measurements of the outcome. The primary results will be the treatment effect estimates at 6 and 12 months and 95% confidence limits.

Other secondary outcomes will be analysed using regression models appropriate for the type of outcome. The effect of CGA on the rate of hospital admission will be tested using a Poisson regression model with a random intercept for study centres and the effect of CGA on time to all-cause mortality and time to hospital admission will be assessed using Cox regression with frailty (random intercepts) for study centres. A detailed statistical analysis plan will be made public before unblinding of the trial statistician and other study personnel at the coordinating centre.

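### The admission-rate model has a centre intercept but no patient-level dispersion term; if admissions are overdispersed and sites differ in size, it gives up some precision that a negative binomial model would keep

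*Protocol article*

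**What the plan says.** Section {20a} of the protocol article fixes the model: the admission rate is to be "tested using a Poisson regression model with a random intercept for study centres". For this outcome it names no dispersion parameter, patient-level random effect or robust variance. Robust standard errors appear only for the primary GAS analysis, and within-patient correlation is modelled only for the repeated continuous outcomes. The same section states: "Data will be analysed at the individual patient level".

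The outcome is listed among the secondary objectives in Table 2 as "Hospital admissions (number and reason"), over a follow-up described in section {13} as "All participants will be followed up by their respective hospitals for a total of 12 months".

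Two design features bear on the point. Treatment does not vary within a hospital, since "randomisation at the cluster (hospital) level has been chosen to avoid contamination of the intervention" (section {8}). Section {14} plans for very unequal sites, with an "average cluster size of 20 participants (coefficient of variation of sizes = 1"), and states that this "would require 16 hospital sites (clusters) with 8 sites in the intervention and control arm", respectively.

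**The concern.** Repeat admissions often cluster in a minority of patients. The eligibility criteria admit CKD stage 3 through dialysis with any Frailty Index above 0.25, so a wide spread of admission risk is plausible here. A Poisson model has no room for such a spread within a centre. The only extra variance it has is one centre variance, common to all sites.

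Patient heterogeneity adds to the variance of a site's rate in proportion to 1/n, where n is the number of patients at the site. A true centre effect adds the same amount whatever the site size. If one common variance has to stand for both, small sites receive too much weight and large sites too little. The rate ratio is then less precise than the data allow. Admissions are a stated secondary objective and also feed the safety monitoring, and there are only 16 clusters, so avoidable loss of precision is worth a look.

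**Working it through.** **The plan's own figure.** The protocol gives no planning figure for admissions. Its GAS power figure reproduces with the stated CV of 1 (two-sided 5% assumed):
- L = 20×0.3/(20×0.3 + 0.7) = 0.896
- Relative efficiency = 1 − 1²×0.896×0.104 = 0.906
- Design effect = (1 + 19×0.3)/0.906 = 7.39
- Clusters per arm = 2×(1.960 + 1.282)²×7.39/20 = 7.77, rounded up to 8. Power at 8 per arm is 90.8%.

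So unequal site size is a real planning input.

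**Why the Poisson model cannot separate the two sources.** Treatment is constant within a centre. Given the centre effect, the Poisson likelihood depends on the data only through each centre's total admissions and total follow-up time. The spread of counts between patients within a centre drops out.

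**Weights.** Let μ be the yearly admission rate, α the patient dispersion (0 for Poisson) and σ² the true centre variance. For a site of n patients:
- True variance of the log site rate: σ² + (1/μ + α)/n
- Variance the Poisson model works with: s² + 1/(μn), where s² is its inflated centre variance

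Take μ = 1.5, α = 1 and σ² = 0.05, with s² = 0.069 (the simulated median below). Compare sites at half and twice the target of 30:
- Truth: n = 15 gives 0.05 + 1.667/15 = 0.161; n = 60 gives 0.05 + 1.667/60 = 0.078. The large site deserves 0.161/0.078 = 2.1 times the weight.
- Poisson model: 0.069 + 0.667/15 = 0.113; 0.069 + 0.667/60 = 0.080. It gives the large site only 1.4 times the weight.

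**Simulation.** 800 trials per scenario, no treatment effect, 8 + 8 centres, 1.5 admissions per year, gamma-Poisson counts. Both models were fitted by maximum likelihood with a centre intercept. Unequal sites had a realised CV of about 0.88. Rate, dispersion and centre variance are all assumptions, because the protocol gives none of them. Excess variance is 1/(NB-to-Poisson variance ratio) − 1.

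| Mean size | Sites | True centre variance | Dispersion | Median estimated centre variance, Poisson / NB | NB/Poisson variance ratio | Poisson excess variance | Type I error (z), Poisson / NB |
|---|---|---|---|---|---|---|---|
| 30 | unequal | 0 | 1 | 0.021 / 0.000 | 0.825 | 21% | 9.2% / 4.5% |
| 30 | unequal | 0.05 | 1 | 0.069 / 0.025 | 0.957 | 4.5% | 10.0% / 9.4% |
| 30 | unequal | 0.05 | 2 | 0.112 / 0.019 | 0.923 | 8.3% | 7.9% / 9.5% |
| 30 | unequal | 0.1 | 1 | 0.116 / 0.065 | 0.973 | 2.8% | 11.1% / 10.6% |
| 30 | unequal | 0.3 | 1 | 0.285 / 0.224 | 0.996 | 0.4% | 11.1% / 11.6% |
| 30 | equal | 0.05 | 1 | 0.065 / 0.032 | 0.999 | 0.1% | 10.0% / 9.2% |
| 20 | unequal | 0.05 | 1 | 0.082 / 0.020 | 0.964 | 3.7% | 9.4% / 10.6% |
| 20 | unequal | 0.05 | 2 | 0.139 / 0.003 | 0.867 | 15.3% | 7.4% / 6.8% |

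A second set (1,200 trials per scenario, mean size 30, CV 1, rate 1.5) gave a Poisson variance larger by the following amounts for dispersion 1 and 2:
- site variance 0: 21% and 36%
- site variance 0.02: 10% and 21%
- site variance 0.05: 3% and 8%

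Type I error in that set, Poisson against negative binomial, was 8.6–10.0% against 4.3–5.6% at site variance 0, 9.0–10.3% against 8.2–8.6% at 0.02, and 7.1–9.2% against 8.7–10.8% at 0.05.

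A third set (mean size 30, rates 1.0 to 1.5, dispersion 1 to 2) gave an excess of 5–21% at CV 1 and 3–9% at CV 0.5.

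**The case against.** Every input that drives the size is assumed: the protocol gives no admission rate, dispersion or between-centre variance for admissions. The largest losses need no variation at all between 16 hospitals that section {9} describes as a mix of tertiary and peripheral. The CV of 1 is a power-calculation input, while the same section aims for about 30 patients at each site. With milder imbalance the loss shrinks: an analytic check at mean size 30, rate 1.5 and site variance 0.05 gives 2.5% at CV 0.5 and 0.8% at CV 0.3 for dispersion 1 (5.8% and 2.0% for dispersion 2). All of this stands, and it limits the point to a modest, conditional gain.

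It can also be said that dispersion belongs in the analysis plan, which is promised but not shown, and that section {20a} says in general terms that models will suit the outcome. That plan may indeed add a dispersion term. But the next sentence of {20a} names the Poisson model, so this is a stated choice rather than an omitted detail.

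A reader might infer the stronger claim that the planned test is invalid, or that its confidence intervals are too narrow in general. That is not supported. The centre intercept absorbs the overdispersion, so the gross false-positive inflation of a plain Poisson model does not arise. Away from zero site variance, neither model is consistently better on type I error; both run high with a z test on 16 clusters. With a t reference on 14 degrees of freedom, Poisson gives 5.5–8.0% and negative binomial 3.0–9.4%. The negative binomial fit also tends to underestimate the centre variance, as the table shows.

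**Conclusion.** The point holds as an efficiency issue on one of several unranked secondary outcomes. If admissions are overdispersed between patients, the planned model weights unequal sites too equally. The variance of the log rate ratio is then about 3 to 20% larger than under a negative binomial model for site variance 0.02 to 0.1 and size CV 0.5 to 1. In standard-error terms that is about 1.5 to 10% (√1.03 = 1.015, √1.20 = 1.095). The loss is about 20 to 36% of variance at site variance 0, and near nil when sites are equal in size or site variance is large. A clear type I error disadvantage (about 9% against 4 to 5%, z test) is confined to site variance near zero, and nothing in the protocol shows that this is the situation here. These sizes rest on an assumed 1.0 to 1.5 admissions per year, dispersion 1 to 2 and a mean of 30 patients at 16 sites. The primary analysis is not affected.

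**What to change.** In section {20a} and in the analysis plan, before unblinding, replace the Poisson model for the admission rate with negative binomial regression, or with Poisson regression plus a patient-level random intercept. Keep the random intercept for study centres. State log follow-up time as the offset; analysing a rate already implies it, and the 33% allowance for loss to follow-up makes it worth writing down. Keep the planned Poisson model as a sensitivity analysis. The cost is one line of text and one extra parameter. The gain is modest and fades as between-site variation grows, so this is a cheap improvement rather than a necessary correction.

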#### Cost-effectiveness evaluation

For the assessment of cost-effectiveness, a cost-utility analysis will be undertaken with the primary analysis from the perspective of the healthcare system. An incremental cost-effectiveness ratio (CER) per quality adjusted life years (QALY) gained in the intervention arm, compared with the usual care arm, will be calculated following the formula:$$\mathrm{CER}=\frac{{\mathrm{Cost}}_{\mathrm{int}}-{\mathrm{Cost}}_{\mathrm{cont}}}{{\mathrm{QALY}}_{\mathrm{int}}-{\mathrm{QALY}}_{\mathrm{cont}}}$$where int = intervention group (receiving CGA) and cont = control group (receiving usual care).

Cost of the intervention will be calculated based on additional time over usual care for the nurse and geriatrician to complete their assessments. Costs specific to the research (e.g. research assessments) will not be included. Cost of health care usage in the intervention and control group will be calculated from diaries filled out by participants and from hospital records where available. Unit costs of care will be derived from appropriate sources for the care. For primary care, the Medicare schedule with out of pocket will be applied and average Australian Refined Diagnosis Related Groups (AR-DRG) applied for hospital stays. Other costs will be applied at appropriate wage standards for the care provided.

Utility scores will be derived from the EQ-5D-5L [62] using the Australian algorithm if available (unpublished) or the UK algorithm [63]. Quality-adjusted life years for each group will be calculated using the utility score multiplied by time in the study.

Sensitivity analyses will be conducted for cost variations, intervention durations, as well as EQ-5D-5L score variations. Additional analyses will be conducted should there exist cluster effect and variation across sub-groups (e.g. study location, gender, age, frail levels and other relevant comorbidities). Reporting of the cost-utility analysis will follow the Consolidated Health Economic Evaluation Reporting Standards (CHEERS) guideline [64].

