### Plans to promote participant retention and complete follow-up {18b}

Participant retention will be achieved by several strategies. Participant involvement throughout the trial development, activation and conduct, facilitated primarily by obtaining the Consumer Advisory Board’s input, ensures a patient-centred approach is applied to all trial activities and interactions with trial participants. The study staff at each site will be accessible to participants to answer their questions and respond to any concerns. To minimise the burden on a participant’s time, study visits will be scheduled to occur with any pre-existing clinic or other outpatient appointments in place for them when possible. Parking vouchers or travel reimbursements, to a maximum of $60 AUD, will be provided for visits that are study-specific and cannot be done remotely over the phone. Practical guidance and suggestions for participant retention awareness training will occur at the site initiation meetings and is documented in the Operations Manual.

For participants who withdraw from the trial, no further information will be collected from the date of withdrawal. If a participant at an intervention site does not receive the CGA, or a participant at the control site receives a CGA, they will remain in the trial and be followed up until the end of the study and analyses will be conducted using the intention-to-treat principle.

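### QALYs defined as utility times time in the study stop accruing when a living patient withdraws, so the cost-effectiveness ratio can be biased if attrition differs by arm or if costs and QALYs cover different periods

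*Protocol article*

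**What the plan says.** Cost-effectiveness is a secondary objective in Table 2 of the protocol article. The section Cost-effectiveness evaluation divides the between-arm cost difference by the between-arm QALY difference and defines the QALY in one sentence: "Quality-adjusted life years for each group will be calculated using the utility score multiplied by time in the study".

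Four other statements bear on that sentence:

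- Participant timeline {13} sets the horizon: "All participants will be followed up by their respective hospitals for a total of 12 months".
- Table 2 schedules the EQ-5D-5L at "Baseline, 3, 6 and 12 months".
- The retention section {18b} says: "For participants who withdraw from the trial, no further information will be collected from the date of withdrawal".
- Sample size {14} plans for substantial attrition: "an allowance for a 33% loss to follow-up over the 12 months was included, requiring baseline GAS observations from 478 participants".

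The economic sensitivity analyses vary costs, intervention duration and EQ-5D-5L scores. They do not name attrition. Section {20c} adds a general sensitivity analysis that imputes values missing at random and does not mention QALYs or costs.

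**The concern.** For a patient who dies, ending accrual when time in the study ends is correct. For a patient who withdraws alive it is not: health continues, but the rule credits nothing for the rest of the 12 months. The rule does not distinguish the two cases.

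There is a second gap. Utility is measured four times, but the sentence refers to the utility score without saying whether that is the baseline value, the last value, a plain mean or a time-weighted average.

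What is at stake is the denominator of the ratio. QALY differences over 12 months are usually small, so a small error from follow-up time can change the ratio materially. Clinicians and participants are unblinded ({17a}), so different withdrawal rates by arm are plausible, though the article gives no figure for them. The assessment takes place within 14 days of the baseline goal-setting ({11a}), so its cost is mostly incurred before any later withdrawal, while the QALYs of those who leave are cut short.

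**Working it through.** **The plan's own figure.** The article gives no QALY figure. Its only figure on attrition is the inflation of the sample size. It starts from "This power calculation, giving a sample size of 320" and allows 33% loss: 320 / (1 − 0.33) = 477.6, rounded up to 478. This reproduces exactly. The 33% does not separate deaths, missed visits and withdrawals, so for living patients who leave it is an upper limit.

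**Inputs.** From the article: 12-month horizon; loss d up to 0.33; EQ-5D-5L at 0, 3, 6 and 12 months. Assumed: constant utility u = 0.60; mean exit time t = 0.25, 0.50 or 0.75 years; all leavers alive; an attrition imbalance of 10 percentage points.

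**Formula.** Under the written rule, arm mean QALY = u × [(1 − d) + d × t]. The full 12-month value is u. The shortfall is u × d × (1 − t), which is a fraction d × (1 − t) of the full value.

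**(a) Level in one arm, d = 0.33, correct value 0.600**

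| Mean exit | Written rule | Too low by |
|---|---|---|
| 3 months | 0.60 × (0.67 + 0.0825) = 0.452 | 25% |
| 6 months | 0.60 × (0.67 + 0.165) = 0.501 | 16.5% |
| 9 months | 0.60 × (0.67 + 0.2475) = 0.551 | 8% |

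The shortfall is proportional to the share who leave alive. If only half of the 33% were living leavers, it would fall from 0.050–0.149 QALY to 0.60 × 0.165 × (0.25 to 0.75) = 0.025–0.074 QALY.

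**(b) Equal attrition, no true effect.** Both arms lose the same amount and the difference is 0. There is no bias in the QALY difference.

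**(c) Unequal attrition, no true effect.** With 33% in control and 23% in intervention, the false difference is u × 0.10 × (1 − t):

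- exit at 3 months: 0.60 × 0.10 × 0.75 = +0.045
- exit at 6 months: 0.60 × 0.10 × 0.50 = +0.030
- exit at 9 months: 0.60 × 0.10 × 0.25 = +0.015

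The opposite imbalance (28% control, 38% intervention) gives the same sizes with a negative sign. The result scales with utility: at u = 0.50 the range is 0.0125 to 0.0375, and at u = 0.70 it is 0.0175 to 0.0525.

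**(d) Equal 33% attrition, true gain 0.030.** The written rule gives 0.030 × 0.7525 = 0.023, 0.030 × 0.835 = 0.025 or 0.030 × 0.9175 = 0.028. If incremental cost is not truncated, the ratio rises by 1/0.7525 = 1.33, 1/0.835 = 1.20 or 1/0.9175 = 1.09.

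**(e) Which utility score, no attrition.** Compare two assumed intervention paths at 0, 3, 6 and 12 months with a flat 0.60 control. The area for the first path is 0.25 × 0.65 + 0.25 × 0.675 + 0.50 × 0.625 = 0.644, a gain of 0.044. For the second it is 0.25 × 0.60 + 0.25 × 0.625 + 0.50 × 0.675 = 0.644, also a gain of 0.044.

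| Path | Area gain | Baseline × time | Last × time | Plain mean × time |
|---|---|---|---|---|
| 0.60, 0.70, 0.65, 0.60 | 0.044 | 0.000 | 0.000 | 0.0375 |
| 0.60, 0.60, 0.65, 0.70 | 0.044 | 0.000 | 0.100 | 0.0375 |

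The same area gain can be reported as anything from 0.000 to 0.100, depending on a choice that the sentence leaves open.

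**The case against.** The strongest defence is that the sentence is shorthand. Utility multiplied by time is the generic description of a QALY, and a trapezoidal area is itself a sum of such products. The article condenses a fuller protocol, and a detailed analysis plan is announced in {20a}. A reader might infer that the plan ignores the path of utility over time. The documents do not support that: the score is undefined, and a time-weighted average over the four visits is a possible reading. What stands is that the sentence does not fix the choice.

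A reader might also infer that baseline utility will not be adjusted for. That would be an argument from silence. The article gives no model for the QALY difference, and {20a} does adjust EQ-5D-5L scores for baseline with a random centre intercept. It is not part of this point.

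The 33% is an allowance for the 12-month goal-attainment analysis. It may include deaths, for whom the rule is right, and patients who miss a visit without withdrawing, whose time in the study need not have ended. Costs may also continue to be captured, since hospital records are a source and the consent covers data linkage ({26b}). If costs were cut short in proportion to QALYs, the ratio might change little. These points limit the size of the problem and make it conditional.

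They do not remove it. The article states a rule for the base case rather than leaving one open. Read with the withdrawal rule, it ends accrual for the living. The general imputation line in {20c} is confined to sensitivity analyses and leaves the base case unchanged.

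**Conclusion.** The point holds in conditional form. As written, the rule treats a patient who withdraws alive like one who died, and it does not say which utility score applies. The ratio can be biased when attrition of living patients differs by arm, or when the early assessment cost is counted in full against shortened QALYs.

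A reader might go further and conclude that the ratio is biased by attrition in any event. The documents do not support that. With equal attrition and no effect the QALY difference is unbiased, no passage predicts an imbalance, and the direction of any bias cannot be known in advance.

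The sizes, 8% to 25% on arm means and 0.015 to 0.045 QALY for a 10-point imbalance, rest on assumed utility 0.60, assumed exit times, and 33% as an upper limit for living losses. This affects a secondary economic outcome, not the primary analysis. It should be corrected before the economic analysis is run.

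**What to change.** Replace the QALY sentence with a definition per patient: the area under the EQ-5D-5L utility curve over a fixed 12 months, by trapezoid over 0, 3, 6 and 12 months, with utility set to zero only from the date of death. State that patients lost alive are handled in the base case by multiple imputation that respects clustering by centre. Put costs on the same 12-month horizon, so that numerator and denominator cover the same period.

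The change uses data already scheduled for collection. It costs a revised sentence and modest extra analysis work. The imputation relies on a missing-at-random assumption, which cannot be verified from the trial data and should be acknowledged when the results are reported.

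### QALYs defined as utility multiplied by time in the study: read as written, a participant lost while alive stops accruing QALYs as if dead, so unequal loss between arms would bias the cost-effectiveness ratio

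*Protocol article*

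**What the plan says.** Under Cost-effectiveness evaluation, the protocol article makes the between-arm QALY difference the denominator of its main economic measure: "An incremental cost-effectiveness ratio (CER) per quality adjusted life years (QALY) gained in the intervention arm, compared with the usual care arm, will be calculated". It then gives the QALY rule: "Quality-adjusted life years for each group will be calculated using the utility score multiplied by time in the study".

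Three other places bear on it:

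- Participant timeline {13} sets the horizon: "All participants will be followed up by their respective hospitals for a total of 12 months". Table 2 schedules EQ-5D-5L at baseline, 3, 6 and 12 months.
- The retention section {18b} says what happens at withdrawal: "For participants who withdraw from the trial, no further information will be collected from the date of withdrawal".
- Sample size {14} plans for substantial attrition: "an allowance for a 33% loss to follow-up over the 12 months was included".

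On missing data, section {20a} provides multiple imputation for the three-month GAS score only. Section {20c} says that imputation of randomly missing values will be tried in sensitivity analyses. The economic sensitivity analyses cover costs, intervention duration and EQ-5D-5L scores; incomplete follow-up is not among them.

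**The concern.** Ending QALY accrual is right at death, because utility is then zero. It is wrong when a living participant leaves, because that person's utility continues unobserved. A rule that multiplies utility by time in the study treats the two alike.

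Two consequences follow. With equal loss in both arms, both are under-credited and a real gain is diluted. With loss that differs in amount or timing, the difference in observed time is counted as a difference in health.

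The trial is open-label, only intervention participants have the extra CGA visit, and there are eight hospitals per arm, so retention could differ between arms. Costs recorded in participant diaries are cut off at withdrawal too, so the numerator of the ratio can also shift. Cost-effectiveness is a named secondary objective, and the Discussion part of the abstract ties adoption of CGA in routine practice partly to it.

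**Working it through.** **The plan's own figure.** Sample size {14} states "This power calculation, giving a sample size of 320, assumes a common standard deviation of 10 units and an intra-cluster correlation coefficient of 0.3" and then "an allowance for a 33% loss to follow-up over the 12 months was included, requiring baseline GAS observations from 478 participants". Check: 320 / (1 − 0.33) = 477.6, rounded up to 478. This reproduces. The protocol gives no expected utility, QALY difference, dropout timing or split of the 33% between deaths and losses alive. Those inputs are assumptions below, with ranges.

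**One participant.** Utility 0.6, alive throughout, lost at month 6. Full 12-month QALY: 0.6 × 1 = 0.60. Rule as written: 0.6 × 0.5 = 0.30, the same as for a participant who died at month 6.

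**Equal loss: dilution.** Assume 10% die and 23% are lost alive (33% in all, mutually exclusive), each uniformly over the year, so half a year is lost on average. Assume utility 0.65 in control and 0.68 with CGA.

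- Time alive per participant: 1 − 0.10 × 0.5 = 0.95 year. True gain: 0.03 × 0.95 = 0.0285 QALY.
- Time in the study: 1 − 0.33 × 0.5 = 0.835 year. Gain as written: 0.03 × 0.835 = 0.0251 QALY.
- Ratio: 0.835 / 0.95 = 0.879, about 12% too small.

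**Unequal loss: false difference when the truth is zero.** Take no true effect, the same utility u in both arms, the same mean dropout time t (in years), and no deaths. The spurious CGA-minus-control difference is

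(loss in control − loss in CGA) × (1 − t) × u.

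| Imbalance | u = 0.6, t = 0.5 | Range, u 0.5–0.8 and t 0.25–0.75 |
|---|---|---|
| 5 points | 0.05 × 0.5 × 0.6 = 0.015 | 0.05 × 0.25 × 0.5 = 0.006 to 0.05 × 0.75 × 0.8 = 0.030 |
| 10 points | 0.10 × 0.5 × 0.6 = 0.030 | 0.10 × 0.25 × 0.5 = 0.0125 to 0.10 × 0.75 × 0.8 = 0.060 |

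The sign favours whichever arm keeps more participants. A simulation (239 per arm, mean utility 0.6, SD 0.2, uniform dropout times, 33% loss overall, 4,000 runs, no clustering) gave +0.0152 and +0.0302 for 5 and 10 points. The difference in full-horizon QALYs was zero to three decimals in each case.

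**Timing alone.** With equal 33% loss, all alive, but mean dropout at 3 months in one arm and 9 in the other, at utility 0.6: 0.33 × (0.75 − 0.25) × 0.6 = 0.099 QALY. This is an extreme contrast. It shows that equal totals do not guarantee an unbiased difference.

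**Set against a small true gain.** Using the equal-loss inputs (true gain 0.0285), but 18% lost alive with CGA and 28% in control:

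- Rule as written: 0.68 × (1 − 0.05 − 0.09) − 0.65 × (1 − 0.05 − 0.14) = 0.5848 − 0.5265 = 0.058.
- Losses reversed: 0.68 × 0.81 − 0.65 × 0.86 = 0.5508 − 0.5590 = −0.008.

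**The case against.** The strongest reply is that utility multiplied by time is the ordinary short definition of a QALY, and that a journal article may leave to a fuller document how repeated utilities are combined and missing ones handled. That is fair for omitted detail. But this sentence states a rule and names the time quantity, and the retention section ends observation at withdrawal. The other reading, a nominal 12 months for everyone, would fail differently: death would then cost no QALYs. The sentence needs correcting on either reading.

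The planned imputation in sensitivity analyses could expose the problem, but it does not change the main definition.

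Several stronger readings are tempting and not supported:

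- *A third of participants will be lost alive.* The 33% is a sample-size allowance for GAS at 12 months. It may include deaths, and missing a GAS assessment is not the same as leaving the study.
- *The rule will double or reverse the QALY gain.* That needs roughly a 10-point imbalance and a small true gain, both assumed here. The protocol predicts no imbalance, and its retention measures are not arm-specific.
- *There is no common horizon, or only one utility value is used.* The protocol gives 12 months of follow-up and four EQ-5D-5L assessments. The QALY sentence merely fails to use them explicitly.
- *The plan contradicts itself because EQ-5D-5L scores* "will be analysed using mixed models for repeated measures (MMRM"*).* That model targets mean scores at visits, whereas a QALY is cumulative. They are different quantities, and no missing-data assumption is stated for EQ-5D-5L.

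**Conclusion.** The point holds as a defect in a stated rule: taken as written, loss while alive is scored like death. Equal loss costs about 12% of a true gain under the assumed 10% deaths and 23% losses alive. Each 10 points of arm imbalance adds a false difference of about 0.030 QALY (0.0125 to 0.060), and each 5 points about 0.015, on assumed utilities and dropout times. If fewer participants are lost alive than the 33% allowance would permit, dilution is smaller; if loss is balanced in both amount and timing, there is no appreciable false difference under no true effect.

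The effect is confined to the secondary cost-effectiveness analysis and does not touch the primary GAS comparison. Severity: should-fix.

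**What to change.** Replace the QALY sentence with wording such as: *QALYs will be calculated per participant over a fixed 12-month horizon as the area under the EQ-5D-5L utility curve (baseline, 3, 6 and 12 months), with utility 0 only from the date of death. Utilities and costs missing after loss to follow-up while alive will be multiply imputed, using a model that includes arm, accounts for hospital clustering and allows for unknown vital status after withdrawal. A missing-not-at-random sensitivity analysis will be reported. Mean QALYs per participant will be reported by arm.*

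The vital-status clause is needed because no information is collected after withdrawal, so some participants may die unobserved within the 12 months. Reporting means per participant also settles what is meant by QALYs for each group.

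No new assessments are needed: the four EQ-5D-5L measurements and mortality are already collected. The cost is a little more analysis work and a main analysis that relies on a missing-at-random assumption, which is why the sensitivity analysis belongs with it. The change should be made before unblinding.
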